## Abstract

**Background:**

The proportion of people aged 65 or older is the fastest growing age group worldwide. Older adults in aged care facilities have higher levels of depression, and lower levels of social support and sense of belonging compared with older adults living in the community. Research has begun to assess the effectiveness of interventions to improve the mental health of residents and has found both cognitive and physical benefits of video game playing. The benefits of playing these games in a group may also lead to greater social interaction and decreased loneliness. The current study aims to investigate an intervention program designed to foster relationships among older adults in care based on shared interests. Residents will be assessed on the effectiveness of a 6 week program of playing Wii bowling in comparison to a control group.

**Method/Design:**

Participants will be allocated to the intervention (Wii bowling) or the control group based on their place of residence. Participants in the intervention group will be invited to participate in Wii bowling twice weekly, with up to three other residents for a period of 6 weeks. Residents in both conditions will be assessed for depression, social support, sense of belonging, and current self-rated mood at pre-intervention (0 weeks), post-intervention (6 weeks), and at 2-month follow up (14 weeks). Qualitative data on social interaction between group members will also be collected at weeks 1, 3, and 6. Both groups will receive a Wii console after week 6 to establish if residents and staff engage with the Wii without intervention.

**Discussion:**

The Wii provides a user friendly platform for older adults to use video games, and it incorporates both social and competitive aspects in the game play. Existing research has not extensively investigated the social aspects of using this type of technology with older adults. If found to be effective, incorporating Wii games into an activity schedule may benefit the mental health of older adults living in care by establishing an intervention that is fun, economical, and easy to use.

**Trial Registry:**

Australian New Zealand Clinical Trials Registry: ACTRN12614000445673

## Background

The World Health Organisation has estimated that the global population of older adults will grow by 223% by the year 2050 [1]. In 2050 it is estimated that there will be 2 billion older adults, of which 80% are expected to be living in developing countries [1]. Due to the increasing time spent in old age and the high level of disability in older adults, there is an increasing need for residential aged care facilities, community care, and flexible care services [2].

Older adults in residential care are at an increased risk of a number of mental health disorders when compared to community samples. Research indicates that 40.5% of residents in high level care and 25.4% of residents in low level care experience depression [3]. Older adults are also at risk of experiencing loneliness, with approximately 10% of older adults in care reporting frequent loneliness [4]. Harper [5] has found that the aged care environment does not promote well-being or the formation of meaningful friendships even though residents are often with other people. Loneliness in older adults is strongly associated with higher levels of depression, even after controlling for variables such as gender, age, ethnicity, education, income, marital status, social support, and perceived stress [6, 7]. Older adults in residential care are at an increased risk of a number of mental health disorders even though residents are in an environment that has been designed to provide social support, alleviate boredom, and decrease loneliness along with providing medical support. Knight and Mellor [8] have proposed that a combination of unfulfilling social activities and constant interactions with unfamiliar people can lead to the development of poor mental health in aged care residents.

Low levels of sense of belonging have been implicated in the poor mental health of older adults who live in aged care facilities [9]. Recent research has shown that sense of belonging partially mediates the relationship between place of residence and depression in older adults, with living in assisted living facilities being associated with lower levels of belonging [9]. Lower levels of belonging is, in turn, associated with higher levels of depressive symptoms [9]. Other research has indicated that residents feel that they do not fit in with those around them, despite aged care providers believing that the provision of a range of social activities facilitates a sense of belonging among residents [8]. The above research highlights the importance of sense of belonging to the well-being of aged care residents and emphasises the need for interventions to enhance a sense of belonging within the aged care environment. Increasing the levels of sense of belonging should be associated with an increase in the overall psychological health and wellbeing of residents [10].

### Gaming

Video games can provide older adults with a number of physical and psychological benefits. Video games are not just used for fun and entertainment. The term “serious gaming” has been used to identify games used for purposes such as education, training, advertising, research, and health promotion [11]. Recently, games have been developed that also incorporate the use of the whole body. These games have been termed “exergames” as they can improve health, physical fitness, and coordination through the combination of physical activity and game play [11]. A systematic review of the physical and cognitive effects of older adults playing physically interactive computer games was conducted [12]. Across 12 studies it was found that interactive computer games were safe, and are an effective way to increase physical activity in older adults. The use of the computer games was also associated with improvements in a range of physical and cognitive outcomes, including self-esteem [13], confidence [14] and balance [15].

A popular game console that is used with older adults is the Nintendo Wii. The Wii is able to track spatial movements and incorporate this into game play [16]. The cost effectiveness of commercial systems such as the Wii make this a feasible option for aged care facilities [17]. Marston [18] found that the Wii console was easier for older adults to use when compared to other more traditional digital games.

The Wii has been shown to be of benefit to older adults who are suffering from sub-syndromal depression. Rosenberg et al. [19] conducted a pilot study with community living older adults with sub-syndromal depression. At the end of three months, participant’s levels of depression decreased and there was an increase in quality of life. Kahlbaugh, Sperandio, Carlson, and Hauselt [20] investigated the effects of playing the Wii on physical activity, loneliness, and mood with older adults in a residential facility. Residents were asked to either play Wii games of their choice or watch television with an undergraduate student. It was found that the group playing Wii had a decrease in loneliness whereas the group watching television had an increase in loneliness by the end of week 10. There was no overall change in negative mood or physical activity levels over the 10 weeks, however during each week there was a non-significant increase in reported positive mood [20].

Playing Wii has also been found to improve the physical activity levels and psychological quality of life when compared to a control group [21]. Residents were asked to play a variety of Wii sports games over 8 weeks. Analyses of the group interview data indicated that residents found the games fun and provided an avenue for greater socialization. By week 8, residents' overall quality of life had improved in the domains of psychological and physical health [21]. In another study using the Wii, participants were divided into three groups, playing Wii with others, playing Wii alone, and a control group who played board games [22]. At the conclusion of the study, the residents in the Wii conditions scored significantly higher on self-esteem, physical activity, and positive affect, and significantly lower on loneliness when compared to the control group. No difference was found between the groups playing Wii alone and with others [22].

No previous study has systematically measured the effect of using the Wii on depression, sense of belonging, or social support. Social interaction has been measured previously at the conclusion of the intervention, but not throughout the intervention [21]. Depression is a significant issue for residents' well-being, along with a lack of social support and belonging within care facilities. Playing the Wii console is a potential intervention to increase the overall psychological health of residents. Further, no study has utilised a control group to test the use of the Wii console in care facilities measuring depression, social support, and a sense of belonging as the outcome measures.

### Study aims

The aim of the current research is to investigate the mental health of aged care residents (aged 65 years or older) who are encouraged to participant in a group activity involving the Wii console. Participants will be allocated to either an intervention group that involves playing Wii bowling with other residents or to a control group who do not participate. The primary aim of the study is to examine the effectiveness of the Wii to decrease the level of depressive symptoms and increase a sense of belonging, increase self-reported mood, and increase social support at post-intervention and 2-month follow up. A secondary aim of the intervention is to increase the level of social interaction between participants.

## Methods/Design

### Study design

This trial will utilise a mixed-methods, quasi-experimental trial design where an active Wii intervention will be compared to a control (wait condition) utilising aged care facility residents. Residents allocated to the Wii intervention condition will be asked to play Wii bowling for 6 weeks. Those residents in aged care facilities allocated to the control condition will not have access to the Wii intervention during the first 6 weeks. The intervention group will be compared to residents in an aged care facility  with no intervention. All participants meeting inclusion criteria will be assessed using paper and pen surveys at pre-intervention (week 0), post-intervention (week 6), and 2-month follow up (week 14). Qualitative interval analysis will also be conducted throughout the intervention (weeks 1, 3 and 6). The aged care facilities for both the control and intervention group will be provided with the Wii and instructions for use to encourage free play after week 6 (Fig. 1, Flow chart of study design). Recruitment began on 25 November 2013 and continued until November 2014.

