### Control group

The control group participants will be located in two different aged care facilities. The control group will not take part in any activities involving the Wii console in the first 6 weeks. The control and intervention group will be provided with a Wii console and staff training on how to play Wii bowling at the end of the 6 week intervention period.

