### Hypotheses

It is hypothesised that participants in the active Wii condition will demonstrate greater improvements in mood, depression, social support, and sense of belonging, in comparison to those in the control condition. Those in the active Wii condition are hypothesised to also maintain their improvements at the 2 month follow-up. In addition, it is hypothesised that those participants in the active Wii intervention will demonstrate higher levels of within group, positive group interactions from pre to post-intervention.

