### Statistical analysis

To establish if there are any significant differences between the intervention and the control group on levels of dementia (SLUMS exam), residents' age [30], and length of time in care [31], between groups *t*-tests will be conducted. A series of chi-square tests will be conducted to establish if there are differences between groups and the demographic variables of relationship status, level of education, self-rated health status, and gender. The intervention and control groups will be compared in relation to pre, post, and follow-up changes in depression, sense of belonging, social support, and mood using a mixed model between groups multivariate analysis of variance conducted using SPSS v20.

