## Discussion

This research aims to identify if playing Wii bowling can benefit aged care facility residents by improving their overall psychological health. Older adults who reside in aged care facilities have higher level of depression [3], and lower levels of sense of belonging [9] and social support [33] than older adults who remain living in the community. If successful, this intervention may also lead to an increase in social interaction between residents. This research may benefit staff in aged care facilities by establishing an intervention for mental health issues that is fun, economical, and easy to use.

The proposed program enables participants in the intervention group to increase their overall sense of well-being, with the potential to increase their sense of belonging. It is expected that participation in the intervention program will also enable residents to learn new skills and also help to facilitate shared relationships within the facility. All aged care facilities involved will also be provided with a Wii console, which will remain in the facility at the end of the initial 6 week research program. The control group and intervention group will have access to a Wii console at the end of the week 6. Both groups will be shown how to play the Wii independently, and staff will be provided with training. The results will improve our understanding of sense of belonging, mood, depression, and social support in the aged care facility residents, and potentially provide a cost-effective and scalable method of improving mental health in this population.

Potential limitations have been identified. Participation in the Wii intervention may not help to alleviate overall loneliness and depression in older adults. Harper [5] has found that the aged care environment does not promote well-being or the formation of meaningful friendships. Participation in a group activity may be enjoyable for the residents involved, but the activity may not alleviate overall symptoms of depression in aged care residents. Residents are also not selected based on depression symptoms, so a floor effect may occur. To address this potential limitation, qualitative data collected through verbatim written transcripts and the post-intervention evaluation questionnaires will be used to ascertain if there are any changes in resident’s behaviour throughout the intervention period that may not be captured through the quantitative measures.

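### Control facilities receive the Wii after week 6, so the week-14 difference between arms compares programme plus free access with delayed free access and cannot separate a faded benefit from control catch-up

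*Protocol article*

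**What the plan says.** The control arm is a wait condition. Its residents "will not have access to the Wii intervention during the first 6 weeks" (Study design). After that, both arms' facilities "will be provided with the Wii and instructions for use to encourage free play after week 6". The Control group section says: "The control and intervention group will be provided with a Wii console and staff training on how to play Wii bowling". The Discussion adds: "Both groups will be shown how to play the Wii independently, and staff will be provided with training". The abstract gives the reason for the handover: "to establish if residents and staff engage with the Wii without intervention".

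Outcomes are measured at weeks 0, 6 and 14. The primary aim is to lower depressive symptoms, raise belonging and mood, and "increase social support at post-intervention and 2-month follow up" (Study aims). The Hypotheses section first predicts greater improvement than in the control condition, then states: "Those in the active Wii condition are hypothesised to also maintain their improvements at the 2 month follow-up". For the analysis, "The intervention and control groups will be compared in relation to pre, post, and follow-up changes" in the four outcomes, in one mixed-model multivariate analysis of variance (Statistical analysis). No distinction is drawn there between week 6 and week 14, and the limitations in the Discussion do not mention that controls have the Wii before week 14.

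**The concern.** Week 6 and week 14 carry different between-arm contrasts. At week 6 the control arm has had no Wii. At week 14 its facilities have had a console for 14 − 6 = 8 weeks, with training and with free play as the stated purpose. The primary aim and the planned model nevertheless treat the two times alike.

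The bias runs in an awkward direction: the better the Wii works and the more control residents take it up, the smaller the week-14 difference becomes. A lasting benefit could then be reported as not sustained. Equally, an interaction that is significant because the arms converge after week 6 could be taken as loss of benefit when it reflects control improvement.

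**Working it through.** **1. What each time point contrasts**

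| Time | Wii arm | Control arm | Between-arm difference |
|---|---|---|---|
| Week 6 | six weeks of organised play | no Wii | Wii programme vs no Wii |
| Week 14 | organised play, then 8 weeks of free access | 8 weeks of free access | programme plus free access vs delayed free access |

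**2. The plan's own sample size.** Inputs from Sample Size and power calculations: f(V) = .25, alpha .05, power .80, 79 per condition (N = 158). For a repeated-measures MANOVA interaction of 2 groups by 3 time points, the noncentrality is λ = N·f(V)² = 158 × .0625 = 9.875 with df 2 and 155. Power is .802, and 158 is the smallest N that reaches .80. A global test on four outcomes (4 df) would need 196. The stated number therefore fits a calculation in which week 14 is a full between-arm time point.

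**3. A stand-alone week-14 contrast.** Assumptions, none of them in the protocol: the true effect is d = .5 (2 × .25) and persists in the Wii arm; controls gain a share u of it by week 14; clustering is ignored. The week-14 difference is .5(1 − u). The two-sample t-test noncentrality is .5(1 − u)·√(79/2), with 156 df.

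| u | Difference | Power |
|---|---|---|
| 0 | .50 | .88 |
| .10 | .45 | .80 |
| .25 | .375 | .65 |
| .50 | .25 | .35 |
| 1 | 0 | .05 |

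**4. The omnibus group-by-time test, one outcome.** Same assumptions, with equal correlation r between time points. The between-arm differences at weeks 0, 6 and 14 are (0, .5, .5(1 − u)). With SS their sum of squares about their mean, λ = (79/2)·SS/(1 − r), on df 2 and 155.

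- u = 0: differences (0, .5, .5), SS = .1667; at r = .5, λ = 13.17 and power is .91.
- u = .5: differences (0, .5, .25), SS = .125; λ = 9.875 and power is .80.
- u = 1: differences (0, .5, 0), SS = .1667; power is .91 again.

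For u = 0 against u = .5, power is .78 against .65 at r = .3, and .99 against .96 at r = .7.

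Full catch-up leaves the omnibus test as strong as no catch-up, because a difference that appears at week 6 and vanishes by week 14 is itself an interaction. The test does not tell the two patterns apart; only the week-14 contrast does, and that contrast has two explanations.

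**The case against.** The design is openly a wait-list one, non-access is limited to the first six weeks in plain words, and giving both arms the console has a stated purpose. The week-6 comparison, which is the real test of Wii against no Wii, is untouched. Free play may be much weaker than the organised programme, so dilution could be small; at 10% control gain even the stand-alone week-14 contrast keeps power .80. All of this stands.

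Three stronger readings are tempting and are not supported:

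- *That the maintenance hypothesis cannot be answered.* The sentence on maintenance names no comparator and reads naturally as a change within the Wii arm, which the planned model can estimate. The difficulty lies with the primary aim and the between-group analysis.
- *That the planned test collapses.* The fall from .88 to .35 belongs to a stand-alone week-14 contrast. The omnibus test falls only modestly at partial catch-up and not at all at full catch-up.
- *That use of the console in weeks 6 to 14 goes unmeasured.* The figure listing the instruments is not shown and the article is condensed, so this cannot be established.

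What the objection does not remove is that effectiveness at week 14 is in the primary aim, is compared between arms, and carries no caveat about control exposure.

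**Conclusion.** The point holds as one of interpretation at week 14. The protocol itself fixes the handover, the aim and the comparison, and together they leave a week-14 between-arm difference that is not a comparison with residents who have had no Wii. A small or null difference there is ambiguous between fading and catch-up. The week-6 result is not affected.

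The size depends on control uptake, which the protocol does not give. For the stand-alone contrast, power runs from .88 with no control gain to .05 with full gain; the omnibus test for one outcome at r = .5 stays between .80 and .91. These figures rest on d = .5 persisting in the Wii arm, 79 per arm with complete data, and no clustering. The ambiguity itself needs none of these assumptions.

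**What to change.** - Make the baseline-adjusted week-6 difference between arms the confirmatory comparison, and word the primary aim to match.
- Take week 14 out of the confirmatory test. Report its between-arm difference as secondary, labelled *programme plus free access versus delayed free access*.
- Report maintenance within the Wii arm as the week-14 minus baseline and week-14 minus week-6 changes with 95% confidence intervals. State that this arm also keeps the console, so the estimate has no Wii-free reference and no control for time trends.
- Add control exposure in weeks 6 to 14 to the limitations.

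An analysis split by residents' own reported use after week 6 is not advised: use is self-selected after baseline, so the comparison would be confounded. The fix does not rely on new data collection, since Study design reports recruitment as having run to November 2014 and the week-14 surveys may be largely complete.

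The cost is a change of analysis and wording. The downside is a weaker follow-up claim: within one arm, without a Wii-free comparator.

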**Fig. 1 Fig1:**
[figure not shown]
Flow chart of study design

### Participants

Participants will be recruited from their place of residence with the approval of the aged care facility manager. Four aged care facilities will be sought for participation. Exclusion criteria are: severe cognitive impairment or dementia as assessed by the Saint Louis Mental Status Examination (SLUMS, [23, 24]), diagnosis of bipolar affective disorder, schizophrenia, intellectual disability, severe hearing impairment, acute illness, inability to communicate in English due to non-English speaking background, age of less than 65 years, epilepsy or seizures, pacemaker or implanted medical device or physical disability preventing use of the Wii console. For this research, participants will be excluded if they received a score of 20 or less on the SLUMS exam indicating the presence of dementia or severe cognitive impairment [24]. These exclusion criteria are based on previous research and on the safety precautions provided in the instruction manual from the Wii. Written consent will be gained from both the participants and from the aged care facility manager.

